### **3.10 Study Procedures**

The critical steps for the study period are described in Appendix VII.

#### **3.10.1. Active follow up (first and second)**

##### **Day 0: screening visit/ administration of the study medication**

- 1 Demographic Data and Medical History  
Demographic data and a general history of past and present illnesses will be recorded.
- 2 Informed consent  
A signed informed consent (or thumb-printed whenever the parents/guardians are illiterate) from the parent/guardian shall be obtained before any tests or evaluations related to the study eligibility are carried out. However, a thick blood film before the informed consent can be done as this can be considered a normal procedure for the management of patients suspected having clinical malaria.

3 Physical and Clinical Examination

A general physical examination will be performed (see Appendix I).

A clinical examination will be performed (see Appendix I): symptoms and axillary temperature (electronic thermometer).

4 Vital Signs and Weight

Vital signs (heart rate) and weight will also be measured.

5 Blood Slide

A thick and thin blood smear will be obtained from the subject to verify the presence of *P. falciparum* and to calculate the parasite density. Thick and thin blood films will be prepared, dried and stained with Giemsa stain according to standard operating procedures.

Parasite density will be calculated by counting the number of asexual parasites per 200 leukocytes in the thick blood film, based on an assumed WBC of 8,000 / $\mu$ l by light microscopy at 1000xmagnification. One hundred high-powered fields (HPF) will be examined (independent of presence or absence of asexual parasite stages). The parasite density per microlitre will be calculated using the following formula:

$$\text{Parasite density / } \mu\text{l} = \frac{\text{Number of parasites counted} \times 8,000}{\text{Number of leukocytes counted}}$$

6 PCR

A blood sample will be collected on filter paper (Whatmann 3MM) at day 0 before treatment and on day 1 and, from day 14 onwards, every time a blood slide is done. Samples from patients classified as late treatment failure will be subsequently used for parasite genotyping. An additional blood sample at day 0 will be collected for later determination of the G6PD status. The collection will be carried out only in sites where CDA is tested.

7 Laboratory Tests

Blood haemoglobin, red blood cell count, total white blood cell count, differential count.

Total bilirubin, ALAT and creatinine will be measured.

8 Administration of the Study Drugs

9 Adverse Events Report

All adverse events will be recorded. See section 7.1.4 for the details on the information collected.

10 Concomitant Medications

Any medications taken by the study subject will be recorded in the CRF.

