### **3.8 Follow-up Chart**

All children 6-59 months attending the outpatient clinic with fever or history of fever in the preceding 24 hours will have a thick and thin blood smear done. In sites where CDA is one of

the study drugs, the age range will be 12-59 months old. The parents or guardians of those with a *P. falciparum* infection of the required density will be informed by the health facility staff about the malaria clinical trial and will be requested to freely consent to participate in the trial. Unwillingness or inability to participate will result in the prescription and administration of the local standard treatment regime for uncomplicated *P. falciparum* malaria. The parents or guardians who accept their child to participate in the study will receive detailed explanations about the trial from the study staff. Specifically, they will be informed that three antimalarial drugs are being tested and the option given to the child will be decided randomly (by chance). They will be asked to sign (or thumb-print if illiterate) the informed consent form (see Appendix IV).

For children meeting the inclusion/exclusion criteria, the following steps will be taken:

1. A Case Report Form consisting of demographic and physical/clinical information will be completed;
2. Body weight and axillary temperature will be measured (the latter by using a digital electronic thermometer) and the results will be recorded on the Case Report Form. If the initial temperature value is less than 36°C the measurement will be repeated.
3. A thick blood smear will be obtained for measuring parasite density and a thin blood film for malaria species determination (the sample collected for screening can be used).
4. A blood sample will be collected on Whatman filter paper number 3MM for subsequent genotyping of the infective parasite strains. An additional blood sample to be later analysed for the determination of the G6PD status will be collected from all children in the sites where CDA is tested.
5. Blood sample (2 ml) for haematology/biochemistry will be taken.

At enrolment, children will be assigned a sequential study number. During the first 3 study days (days 0-2) patients will be admitted for observation and study drug administration. Parents/guardians will then be encouraged to return to the clinic for follow up assessments on days 3, 7, 14, 21, 28 and on any unscheduled day if the child is not well.

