All medication will be administered under observation by an authorised member of the study team (physician, clinician, or study nurse).

After the child has reached a study outcome, before or at the end (day 28) of the first active follow up, the parents or guardians will be encouraged to attend the health facility when the child is sick. If the child is not diagnosed with clinical malaria, s/he will be treated accordingly and parents or guardians will be asked to come back again whenever the child is sick. If the child has clinical malaria and meets the inclusion/exclusion criteria, s/he will be treated with the same drug received at the beginning of the first follow up and actively followed for 28 days according to the procedure outlined above. Re-treatment with the same study drug will be done at an interval of at least 29 days from the first treatment, i.e. after the first active follow up has finished. At the end of this second follow up, when one of the study

outcomes is reached, the child will be passively followed up until completion of the 6-month period started at the end of the first active follow up. Any malaria episode will be recorded and the patient treated with the standard antimalarial treatment. No active follow up will be carried out.

Patients will be assessed as summarized in the following flow-chart.

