### 3.9 Selection of the Patients (for the first and second active follow up)

#### Inclusion criteria

In order to be eligible, patients should satisfy the following inclusion criteria:

1. Males and Females aged between 6 months and 59 months inclusive. In the sites where CDA is tested all recruited children will be aged between 12 months and 59 months inclusive. This criterion applies only for the recruitment in the first follow up. For the second follow up, children having been included in the first follow up are eligible, regardless of their age.
2. Body weight of 5 Kg and above.
3. Microscopically confirmed, monoinfection of *Plasmodium falciparum* (parasitaemia  $\geq 2,000/\mu\text{L}$  to  $200,000/\mu\text{L}$ ).
4. Fever (axillary temperature at  $\geq 37.5^\circ\text{C}$ ) or history of fever in the previous 24 hours.
5. Haemoglobin value  $\geq 7.0$  g/dl;
6. Signed (or thumb-printed whenever parents/guardians are illiterate) informed consent

by the parents or guardians. Note the informed consent will be asked only at recruitment and will cover the whole period of the study, including second active follow up and passive case detection.

7. Parents' or guardians' willingness and ability to comply with the study protocol for the duration of the trial.

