### **Exclusion criteria**

Patients with any of the following criteria will not be admitted to the study:

1. Participation in any other investigational drug study (antimalarial or others) during the previous 30 days.
2. Known hypersensitivity to the study drugs.
3. Severe malaria.
4. Danger signs: not able to drink or breast-feed, vomiting (> twice in 24hours), recent history of convulsions (>1 in 24h), unconscious state, unable to sit or stand.
5. Presence of intercurrent illness or any condition (cardiac, renal, hepatic diseases) which in the judgement of the investigator would place the subject at undue risk or interfere with the results of the study, including known G6PD deficiency.
6. Severe malnutrition (defined as weight for height <70% of the median NCHS/WHO reference).
7. Ongoing prophylaxis with drugs having antimalarial activity such as cotrimoxazole for the prevention of *Pneumocisti carini* pneumonia in children born to HIV+ women.

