#### ***3.10.2. Passive follow up (6 months after the first active follow up)***

Patients identified as treatment failures (clinical and parasitological) within the first follow up of 28 days will be treated with a full course of quinine or any other appropriate oral treatment (unrelated to the study drugs). Parents/guardians of children who have either been treated or classified as ACPR, i.e. with no malaria infection at day 28 of the first follow up will be asked to attend the health facility whenever the child is sick for the next 6 months. Each child will be visited monthly at home to keep the contact with the health facility. However, no data or blood slide will be collected unless the child is sick. Any attendance of children belonging to the cohort recruited for the first follow up will be recorded. The child will be clinically assessed and the medical history will be taken. Body temperature and a blood sample for

parasitaemia, Hb and PCR will be systematically collected. A diagnosis will be made and the child treated accordingly. Whenever an episode of uncomplicated malaria is diagnosed, the inclusion and exclusion criteria (section 3.8) will be checked and if these are fulfilled, the child will be re-treated with the same drug received for the first episode and will be followed up for the next 28 days (second active follow-up) with the same methodology as the first active follow-up. After the second active follow up, even if the child attend with an episode of clinical malaria fulfilling the inclusion/exclusion criteria, s/he will be treated with the local first line drug and no active follow up will be carried out after treatment. Children with a malaria infection but not fulfilling the inclusion and exclusion criteria will be treated with the local first line drug and their parents will be informed that they are still part of the cohort under passive surveillance. Children will reach the end of the study at the end of the 6-month passive follow up when they will be visited at home and the parents/guardians will be informed that the study is finished (Appendix VIII).

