## **4. CONCOMITANT THERAPIES**

### ***4.1 Disallowed Concomitant Drug Therapies during the active follow ups***

Any antimalarial, or antibiotic with antimalarial activity (erythromycin or other macrolides, co-trimoxazole or other sulfonamides, any tetracycline including doxycycline, and quinolones, clindamycin). Intake of these drugs leads to withdrawal of the patient from the ongoing active follow up. However, the patient will be kept in the passive follow up and when presenting with another clinical malaria episode fulfilling the inclusion/exclusion criteria, another active follow up can be started. Drugs known to cause haemolysis (e.g. sulpha drugs) should not be administered in children in the CDA arm. There are no disallowed concomitant therapies during the passive follow up.

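### The day-0 G6PD result is not required before a second CDA course, so the text permits avoidable re-exposure of deficient children

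*Protocol*

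**What the plan says.** **Sampling.** Protocol section 3.10.1 (Day 0, item 6) states: "An additional blood sample at day 0 will be collected for later determination of the G6PD status". Section 3.8 describes the same sample as "to be later analysed for the determination of the G6PD status will be collected from all children in the sites where CDA is tested". Neither place gives a due date, a recipient or a use for the result.

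**Eligibility.** Section 3.9 is headed "Selection of the Patients (for the first and second active follow up". Item 5 of its exclusion criteria covers conditions that would put the child at risk or "interfere with the results of the study, including known G6PD deficiency".

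**Re-treatment.** Section 3.8: "Re-treatment with the same study drug will be done at an interval of at least 29 days from the first treatment". Section 3.10.2 has the criteria re-checked at a second episode. If they are met, the "child will be re-treated with the same drug received for the first episode". Otherwise: "Children with a malaria infection but not fulfilling the inclusion and exclusion criteria will be treated with the local first line drug".

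**The risk as the protocol sees it.** Sections 1.1 and 14 name dapsone as a cause of haemolysis, above all in G6PD deficiency. Section 4.1 adds: "Drugs known to cause haemolysis (e.g. sulpha drugs) should not be administered in children in the CDA arm". Section 14 also presents the entry floor of Hb 7 g/dL as a guarantee that a fall cannot reach life-threatening values.

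**The concern.** The exclusion works only if deficiency is known, and the one routine source of that knowledge is a sample with no reporting date. At the first course this cannot be helped under the present design: a sample taken on day 0 and read later cannot inform treatment on day 0. The second course is different. At least 29 days have passed, the blood has been collected and the assay is planned, yet no readable step brings the result to the person deciding on re-treatment.

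The main objective covers repeat as well as single treatment. A deficient child could therefore receive a haemolytic drug a second time when information already within the trial's reach would have excluded that child. This is a safety and eligibility matter and belongs in the protocol rather than the analysis plan. It touches no primary endpoint, error rate or sample size.

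**Working it through.** **1. Who is concerned.** Table 1 lists CDA at Mbarara, Jinja, Tororo, Rukara, Mashesha and Manhiça, which is 6 sites with 170 children per arm.
- CDA arms: 6 × 170 = 1020, which reproduces the figure in section 3.1.
- Children sampled for G6PD: 6 × 510 = 3060.
- Sampled children in the other two arms: 3060 − 1020 = 2040.

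**2. Sequence under the text.**

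| Time | Required | G6PD result required? |
|---|---|---|
| Day 0, first course | sample taken, CDA given | no |
| Days 1–28 | Hb on days 1, 2, 3, 7, 14, 28 | no |
| Day 29 or later, second episode | criteria re-checked; same drug if met | no |

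A result known by then excludes the child and sends the child to the local first-line drug. A result not yet read does neither.

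**3. Illustrative number re-exposed.** The documents give neither input, so both are assumptions. Re-exposed = 1020 × prevalence × re-treatment proportion.
- 5% and 10%: 1020 × 0.05 × 0.10 = 5.1
- 10% and 25%: 1020 × 0.10 × 0.25 = 25.5
- 20% and 50%: 1020 × 0.20 × 0.50 = 102

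These are exposures, before subtracting any child known to be deficient by then. They are not predicted harms.

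**4. Would the withdrawal rule catch them?** Section 5 withdraws study drug after a severe event related to it. Appendix I, Table D grades the absolute Hb: Grade 2 is 7.0–8.9, Grade 3 is 5.0–6.9 and Grade 4 is below 5.0. A fall brings a child to Grade 3 or worse only if entry Hb < 7.0 + fall. For assumed falls:
- 2.1 g/dL: a child entering at 9.1 or above stays at Grade 2 or lower
- 2.5 g/dL: the same from 9.5
- 3.0 g/dL: the same from 10.0

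So a fall of more than 2 g/dL need not be severe by Hb grade. The rule also needs a causality judgement, which section 14 says is difficult in malaria. Section 14 reports Hb back to baseline by day 14 in the cited trial, so re-checking the 7.0 floor at the second episode need not reveal an earlier reaction.

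**5. The Hb guarantee.** Margin from the entry floor to Grade 4 (also the severe-anaemia limit in Appendix V): 7.0 − 5.0 = 2.0 g/dL. A fall of exactly 2.0 from 7.0 stops at 5.0, which is Grade 3. A fall of 2.1 gives 4.9, which is Grade 4. Section 1.1 says falls above 2 g/dL were more likely in deficient children on chlorproguanil-dapsone (section 14 writes 2 or more), with no maximum stated. For assumed falls of 2.1, 2.5 and 3.0, Grade 4 is reached only from entry Hb below 7.1, 7.5 and 8.0.

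**The case against.** The strongest reply is that this argues from silence. Section 3.10 refers the critical steps to Appendix VII, and Appendices VI to VIII are figures not shown here; one could contain a G6PD step. Saying that the assay comes later does not say it comes after day 28. This stands, and it limits the finding to what the readable text requires.

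Second, the sample may be meant for interpreting Hb data, not for screening. Figure 1 covers both follow-ups and marks the G6PD paper on day 0 without the first-follow-up-only footnote that consent carries. The protocol openly treats children of unknown status. That reading is plausible, but section 3.9 still applies the exclusion to the second course, so a result in hand would bear on eligibility.

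Third, the safeguards are substantial. Exclusion item 5 lets the investigator refuse re-treatment for undue risk, with Hb from days 0 to 28 of the first course available, and this needs no Grade 3 event or causality ruling. Children are admitted on days 0–2, Hb is followed on days 0–3, 7, 14 and 28, a related severe event stops the drug, a DSMB reviews safety, and CDA sites can transfuse. These lower the risk. They do not make the G6PD result available, and a child whose fall went unremarked would still qualify.

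A reader might infer that deficient children will be re-exposed, that 5 to 102 is an estimate, or that the Hb guarantee has been disproved. The documents support none of these: no turnaround is given, both rates are assumed, and no child below 5.0 g/dL is reported.

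**Conclusion.** The gap is real but modest. The readable protocol permits a second CDA course in a deficient child whose day-0 sample has not been read, although the exclusion is meant to apply to that course. It does not show that this would occur. Up to 1020 children are in the arms concerned; how many would be re-exposed cannot be worked out from the documents. The conclusion assumes that the unseen appendices contain no G6PD step, so confidence is medium. The change is worth making because it is cheap: sample, assay and fallback treatment are already in the plan.

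The guarantee in section 14 is a separate, minor wording point. It does not follow from the protocol's own thresholds, and that is all that can be said against it. The haemolysis risk, monitoring and transfusion access are disclosed beside it.

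**What to change.** - **Sections 3.8 and 3.10.1:** require CDA-arm G6PD results to be reported to the site by the end of the first active follow-up (day 28).
- **Section 3.10.2:** require the result to be checked before any second CDA course. Treat a child found deficient with the local first-line drug, through the route already provided for ineligible children. If the result is missing, the investigator decides under exclusion item 5 using the first-course Hb record; the child is not refused automatically.
- **Analysis:** early reading in one arm removes deficient children from CDA only. Repeat the second-episode efficacy and safety comparisons (objectives 3 and 4) in G6PD-normal children of all three arms, whose day-0 samples will exist.
- **Section 14:** replace the guarantee with a statement that entry at Hb 7.0 g/dL or more leaves a 2.0 g/dL margin above the life-threatening level and reduces the risk without removing it.

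The cost is rolling instead of batched reading of up to 1020 samples; the other 2040 can still be batched. Assay location and turnaround are not stated, so some results may be late, and for those children the gap is narrowed rather than closed. The wording change costs nothing.

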**Day 1 and 2: Open Label Treatment Period**

1 Physical and Clinical Examination

A general physical examination and a clinical examination will be performed: symptoms, axillary temperature (electronic thermometer).

- 2 Vital Signs  
Vital signs (heart rate) will be measured.
- 3 Blood Slide  
A thick and thin blood smear will be obtained to verify the presence and to determine the density of asexual and sexual stages of *P. falciparum*.
- 4 PCR  
A blood sample will be collected at day 1 on filter paper (Whatmann 3MM) for later genotyping.
- 5 Concomitant Pharmacological Treatments  
Concomitant medications being taken by the patients will be recorded. For a list of allowed and disallowed medications, see section 4.
- 6 Adverse Events Report  
All adverse events will be recorded. See section 7.1.4 for the details on the information collected
- 7 Laboratory Tests  
Blood haemoglobin in sites where CDA is one of the study arms.
- 8 Administration of the Study Drugs

### **Day 3: Open Label Treatment Period**

- 1 Physical and Clinical Examination  
A general physical examination and a clinical examination will be performed: symptoms, axillary temperature (electronic thermometer).
- 2 Vital Signs  
Vital signs (heart rate) will be measured.
- 3 Blood Slide  
A thick and thin blood smear will be obtained to determine the presence and the density of asexual and sexual stages of *P. falciparum*.
- 4 Concomitant Pharmacological Treatments  
Concomitant medications being taken by the patients will be recorded. For a list of allowed and disallowed medications, see section 4.
- 5 Adverse Events Report  
All adverse events will be recorded. See section 7.1.4 for the details on the information collected
- 6 Laboratory Tests  
Blood haemoglobin, red blood cell count, total white blood cell count, differential count.

### **Day 7, 14 and 21: Open Label Treatment Period**

As Day 3. In addition, the following information will be collected:

- 1 Medical History  
Symptoms and other relevant episodes between visits will be recorded.
- 2 Laboratory Tests  
Total bilirubin, ALAT and creatinine will be measured. At day 14 only if abnormal at day 7. No haematology or biochemistry done at day 21.
- 3 PCR  
A blood sample will be collected on filter paper (Whatmann 3MM) starting from day 14 onwards for later genotyping.

### **Day 28: Open Label Treatment Period**

As Day 7.

- 1 PCR  
A blood sample will be collected on filter paper (Whatmann 3MM) for later genotyping.

### **Unscheduled visits throughout follow up**

During this visits, the same procedures as day 21 will be applied. Hb will be measured if the patient is classified as treatment failure.

The PCR readings will be centralised and masked to the treatment allocation of study subjects, i.e. by personnel different from the treating physician/investigator. In addition, a centralized and independent double-check of a significant percentage of blood slides and filter paper blood samples (PCR) will be carried-out. The percentages of slides and films to be reviewed and the corresponding statistical justifications will be specified in the Statistical Analysis Plan.

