| Treatment               | X              | X              | X              |   |                |                |                |   |                |    |    |                            |

 Spontaneous attendance to health facility;  Only at the beginning of the first follow up.  In sites where CDA is tested, Hb will be determined also at day 1 and 2 after treatment and for the three arms of the study;  If abnormal at day 7.  If patient attends spontaneously the health facility.

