**Figure 1. Follow up chart first and second active follow up.**

| Day                     | 0              | 1              | 2              | 3 | 4              | 5              | 6              | 7 | 14             | 21 | 28 | Any other day  |
|-------------------------|----------------|----------------|----------------|---|----------------|----------------|----------------|---|----------------|----|----|----------------------------|
| History                 | X              |                |                |   |                |                |                | X | X              | X  | X  | X                          |
| Informed consent        | X  |                |                |   |                |                |                |   |                |    |    |                            |
| Examination (clinical)  | X              | X              | X              | X |                |                |                | X | X              | X  | X  | X                          |
| Temperature             | X              | X              | X              | X |                |                |                | X | X              | X  | X  | X                          |
| Blood film              | X              | X              | X              | X |                |                |                | X | X              | X  | X  | X                          |
| Filter paper PCR        | X              | X              |                |   |                |                |                |   | X              | X  | X  | X                          |
| Filter paper G6PD**     | X              |                |                |   |                |                |                |   |                |    |    |                            |
| Adverse drug reactions  | X              | X              | X              | X | X  | X  | X  | X | X              | X  | X  | X                          |
| Concomitant medications | X              | X              | X              | X |                |                |                | X | X              | X  | X  | X                          |
| Haematology             | X              | X  | X  | X |                |                |                | X | X              |    | X  | X                          |

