| Biochemistry*           | X              |                |                |   |                |                |                | X | X  |    | X  |                            |
| Treatment               | X              | X              | X              |   |                |                |                |   |                |    |    |                            |

 Spontaneous attendance to health facility;  Only at the beginning of the first follow up.  In sites where CDA is tested, Hb will be determined also at day 1 and 2 after treatment and for the three arms of the study;  If abnormal at day 7.  If the patient attends spontaneously the health facility.

\*Not all sites; \*\*Only in sites where CDA is tested.

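### For unscheduled visits in active follow-up, section 3.10.1 requires haemoglobin only in treatment failures, while both follow-up charts mark haematology at any spontaneous attendance

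*Protocol*

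**What the plan says.** Section 3.8 of the Protocol foresees illness visits outside the schedule: parents are encouraged to return on the planned days "and on any unscheduled day if the child is not well".

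For these visits, section 3.10.1 (Unscheduled visits throughout follow up) gives this rule: "During this visits, the same procedures as day 21 will be applied. Hb will be measured if the patient is classified as treatment failure". The paragraph for days 7, 14 and 21 in the same section states: "No haematology or biochemistry done at day 21". Under the text, the failure condition is therefore the only route to a required Hb.

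The Synopsis chart and Figure 1 in section 3.8 cover the same period, the first and second active follow-up. Their last column is headed "Any other day 1", and footnote 1 defines it as "Spontaneous attendance to health facility". In the Haematology row of both charts, day 21 is blank and this last column is marked, with no footnote on the mark.

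**The concern.** A site that follows the text and a site that follows the chart will treat the same child differently. The difference falls on the child who returns ill with a negative slide. Every early and late failure criterion in section 3.2 needs parasitaemia, so this child cannot be a treatment failure and has no required Hb under the text.

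This is also a child in whom a low Hb would say something about the drug. Section 14 names haemolysis with dapsone as a concern and notes that malaria itself makes drug-induced haemolysis hard to recognise. Only known G6PD deficiency is an exclusion (section 3.9), and the day-0 sample for G6PD status is analysed later (section 3.10.1, Day 0). Undiagnosed deficient children can therefore receive CDA.

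Hb results are graded for severity (section 7.1.4 and Appendix I, Table D), and adverse events are compared across arms (section 3.6). A safety measurement of this kind should not depend on efficacy failure, or on which page of the protocol a site happens to use.

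**Working it through.** The check is mainly a comparison of the two rules, with a short calculation of the delay.

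**1. The rules side by side**

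| Source | Day 21 | Unscheduled visit | Condition |
|---|---|---|---|
| Section 3.10.1, text | no haematology | Hb | treatment failure only |
| Synopsis chart, Haematology row | blank | marked | none |
| Figure 1, Haematology row | blank | marked | none |

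Read cell by cell over days 0, 1, 2, 3, 4, 5, 6, 7, 14, 21, 28 and the last column, the Haematology row is the same in both charts: marked on days 0 to 3 (days 1 and 2 with footnote 3), blank on days 4 to 6, marked on days 7 and 14, blank on day 21, marked on day 28 and marked in the last column.

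**2. Is the chart mark an implied condition?** The charts footnote other conditions in their cells. Footnote 3 covers the CDA sites: "Hb will be determined also at day 1 and 2 after treatment and for the three arms of the study". Footnote 4 limits day-14 biochemistry to abnormal day-7 results. Footnote 5, on adverse drug reactions on days 4 to 6, reads "If the patient attends spontaneously the health facility". The Haematology mark has no such note, and Biochemistry in the same column is blank.

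**3. Does another section settle it?** Section 3.10.2 collects Hb systematically at sick attendances, but in passive follow-up, which is a different period. It also says the second active follow-up uses the same methodology as the first, so the conflict recurs there.

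**4. Delay under the text rule.** Scheduled Hb at CDA sites is on days 0, 1, 2, 3, 7, 14 and 28 (charts and footnote 3). For a visit on day d between days 8 and 13, the wait is 14 − d:

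- days 8, 9, 10, 11, 12, 13 give 6, 5, 4, 3, 2, 1 days
- mean = (6 + 5 + 4 + 3 + 2 + 1) / 6 = 21 / 6 = 3.5 days, with each day given equal weight

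This window is the relevant one for dapsone. In the trial cited in section 1.1, Hb was back to baseline by day 14, and before day 8 Hb is scheduled on days 0 to 3 and on day 7.

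**5. Endpoints.** The Hb-change endpoint uses days 3, 7, 14 and 28 only (section 3.3), which both rules leave in place. The primary endpoints rest on parasitaemia, clinical signs and genotyping. Appendix V does count Hb below 5.0 g/dL as severe malaria. However, parasitaemia that reappears after day 3 is already a failure with or without fever, so an Hb value could change only its sub-type.

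**The case against.** The strongest case on the other side has four parts.

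- **The chart is a summary.** Section 3.8 introduces it that way, and its last column is loose elsewhere: filter-paper PCR is marked there without condition, although section 3.10.1 (Day 0, item 6) limits those samples to days 0 and 1 and then day 14 onwards. Appendix VII, which section 3.10 cites for the critical steps, is a figure that could not be seen, and neither could the CRF. This stands as a caution: one of those may settle the matter. It does not give sites one rule in the text they can read.
- **Drug exposure is over.** CDA is given on days 0 to 2. With the half-lives in section 1.1 (about 12 h for dapsone and 24 h for chlorproguanil), the six days from day 2 to day 8 are 144 / 12 = 12 and 144 / 24 = 6 half-lives. This stands, and it keeps the point small. It does not remove it, because the protocol gives no time of lowest Hb.
- **Clinicians remain free to act.** Day-21 procedures include a clinical examination and adverse event recording, jaundice is examined and graded (Appendix I), and transfusion is available at CDA sites (section 14). The text does not forbid a clinically indicated Hb. This stands too: the waits apply only if nobody orders a test.
- **Little analytic consequence.** A site's rule applies to all its arms, and the Synopsis plans no formal testing of adverse events. This is largely right. But under the text rule an arm with more failures would have more Hb tests within the same site. The protocol gives no figure from which to size that.

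One could also align the other way, by footnoting the chart cell as treatment failures only. That removes the contradiction but leaves the slide-negative ill child with no required Hb.

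**Conclusion.** The contradiction is real and lies within the protocol text and charts. Its effect is limited to when, and how evenly, low Hb is detected at unscheduled visits in active follow-up. The main window is days 8 to 13 at the six CDA sites, with a wait of 1 to 6 days (unweighted mean 3.5) for a slide-negative ill child. This assumes that the site follows the text, that no clinician orders an Hb, and that visits are spread evenly over those days. It is a minor safety clarification, and no analysis needs to change.

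A reader might infer more, but the documents do not support it:

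- **Longer waits as dapsone harm.** A visit on days 15 to 20 would wait 8 to 13 days, because day 21 has no haematology, and a visit on days 22 to 27 would wait 1 to 6 days. The arithmetic is right, but these days fall after the reported recovery by day 14.
- **A conflict on days 4 to 6.** Both charts give these days their own columns and leave Haematology blank there. A conflict arises only if the last column is read as overriding them.
- **A life-threatening fall.** A drop of more than 2 g/dL from the entry limit of 7.0 would give an Hb below 5.0, which is grade 4. That concerns the entry limit and the size of the fall. Nothing in the protocol places such a fall on days 8 to 13.
- **1020 children affected.** That is the number planned on CDA (6 sites × 170) and only a ceiling. The protocol gives neither G6PD prevalence nor a rate of unscheduled attendance.

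**What to change.** In section 3.10.1, replace the second sentence of the unscheduled-visits paragraph with: *Hb will be measured at every unscheduled visit.* If the sponsor prefers less sampling, the minimum is the same rule at CDA sites only, in all three arms, stated in both text and charts.

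In the Synopsis chart and Figure 1, footnote the last-column Haematology cell as *Hb only*. Without this the cell could be read as the full scheduled panel, which section 3.10.1 gives for day 3 as "Blood haemoglobin, red blood cell count, total white blood cell count, differential count". If the CDA-only version is chosen, say so in the same footnote.

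Do not extend footnote 1 to days 4 to 6. It governs the whole column and would bring in filter-paper PCR on days for which section 3.10.1 does not plan it. If Hb is wanted on those days, footnote the Haematology row alone.

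The cost is one sentence, one footnote in each chart, and a check that the CRF page for unscheduled visits agrees. The downside is one extra Hb per spontaneous visit, which the charts already mark.
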